## Results

Patient recruitment began in April 2024 and is currently ongoing. As of April 10, 2025, 10 patients have been screened, of whom 4 were enrolled. No adverse events or protocol deviations were observed. We expect to complete patient enrollment by March 2026, with a follow-up period of 24 weeks postoperatively. The final data analysis is scheduled to commence in mid-2026.

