## Methods

### Study Design, Participants, and Setting

This is a single-center, open-label, uncontrolled, single-arm, comparative prospective study.

The participants will be patients with open limb wounds transported to our center by ambulance for treatment, with good subcutaneous granulation tissue formation. Furthermore, considering that the area of the skin defect covered by one RECELL 1 kit is 160 cm^2^, we targeted patients with epidermal defects measuring ≥160 cm^2^. Given that the number of such cases transported to our hospital in the past was approximately 5 per year, we decided to target cases over a period of 2 years. The study period will therefore last from April 1, 2024, to March 31, 2026.

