### Data Analysis

This study is designed as a prospective, single-arm pilot study. Given the lack of robust data on RECELL for large traumatic defects, a formal power calculation is not feasible for the primary end point. Therefore, we aim to enroll 10 patients over 2 years, which will provide the descriptive data necessary to inform the design and power calculation for a subsequent randomized controlled trial.

The primary end point is the achievement of ≥95% reepithelialization at the recipient site, assessed at postoperative day 14 (±3 days tolerance), corresponding to the final planned dressing change within the early healing phase (refer to Table 2). We determined that 14 days was appropriate based on our past case experience and several published studies [12-14]. The secondary end points, including the VSS and VAS for scar assessment, will be primarily evaluated at the final observation point of 24 weeks postoperatively (and also at 12 weeks), as detailed in Table 2.

Descriptive analyses for continuous variables will be presented as the mean and SD. Categorical variables will be presented as counts and percentages. Any missing data will be reported, and the analysis will use a complete case analysis approach, given the pilot nature and short follow-up period. Although this is a single-arm pilot study, exploratory comparisons of the primary outcome (reepithelialization rate) and VSS scores will be made against published historical controls to inform the sample size calculation for future randomized controlled trials. Descriptive analyses, including central tendency (mean and median) and variability, will be performed after data collection is completed.

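### The study period, the end of enrolment, the 24-week follow-up and the mid-2026 final analysis cannot all hold

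*Protocol article*

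**What the plan says.** Four statements in the protocol article set the calendar.

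- Study Design, Participants, and Setting: "The study period will therefore last from April 1, 2024, to March 31, 2026". The two years come from the expected caseload, since "the number of such cases transported to our hospital in the past was approximately 5 per year".
- Results, on enrolment and follow-up: "We expect to complete patient enrollment by March 2026, with a follow-up period of 24 weeks postoperatively".
- Results, on timing of the analysis: "The final data analysis is scheduled to commence in mid-2026".
- Study Data Collection, Table 1: the week-24 visit has a tolerance of 14 days either side.

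Three statements in Data Analysis determine what depends on that calendar.

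- The secondary end points, VSS among them, "will be primarily evaluated at the final observation point of 24 weeks postoperatively (and also at 12 weeks"). Table 2 schedules VSS at those two visits only. The primary end point is "assessed at postoperative day 14 (±3 days tolerance").
- For missing data, "the analysis will use a complete case analysis approach, given the pilot nature and short follow-up period".
- The descriptive analyses are to follow the end of data collection.

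**The concern.** The study period and enrolment end in the same month, so the stated study period leaves no room for the last patients' 24-week follow-up. The final analysis then starts about three months later, which is still short of 24 weeks. The last of these dates also conflicts with the article's own rule that analysis waits for complete data.

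Scar quality is part of the stated aim and of the hypothesized key finding. The VSS results are also meant to inform the sample size of a later randomized trial, and week 24 is their main time point. With a target of 10 patients, one or two missing values would matter to a mean and SD. A study team following the printed dates would have to choose between keeping the dates and keeping the follow-up, and the article does not say which takes precedence.

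**Working it through.** **Inputs.** Study period 1 April 2024 to 31 March 2026 (730 days); about 5 cases per year; target of 10; enrolment to March 2026; follow-up of 24 weeks = 168 days, ±14 days; 4 patients enrolled by 10 April 2025, which is 374 days after the start and leaves 355 days. The article gives no exact date for mid-2026, so I take 1 June to 31 July 2026 as an assumed range.

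**The plan's own figure.** 5 per year × 2 years = 10. The target reproduces, and two years is the time needed for accrual alone.

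**Step 1: when is the last week-24 visit?** Treatment date + 168 days, ±14.

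- Treated 1 March 2026: 16 August 2026, window 2 to 30 August.
- Treated 31 March 2026: 15 September 2026, window 1 to 29 September.

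The second date is 168 days after the stated study end and 77 days (11 weeks) after 30 June.

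**Step 2: what last treatment date would make the stated dates work?** Cut date − 168 days for the nominal visit; cut date − 154 days if the visit is made at the earliest permitted day.

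| Data cut | Last treatment, nominal visit | Last treatment, earliest permitted visit |
|---|---|---|
| 31 March 2026 | 14 October 2025 | 28 October 2025 |
| 1 June 2026 | 15 December 2025 | 29 December 2025 |
| 30 June 2026 | 13 January 2026 | 27 January 2026 |
| 31 July 2026 | 13 February 2026 | 27 February 2026 |

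Even the most generous combination (31 July, earliest permitted visit) excludes every treatment in March 2026.

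**Step 3: how many patients would be affected if a cut were enforced?** Let d be the days from the last workable treatment date (nominal visit) to 31 March 2026. Three accrual assumptions, each uniform over time:

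- A: 10 patients over 730 days, 10 × d/730.
- B: the remaining 6 patients over the remaining 355 days, 6 × d/355.
- C: the observed pace, (4/374) × d. This projects 4/374 × 730 = 7.8 patients in all, not 10.

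| Data cut | d | A | B | C |
|---|---|---|---|---|
| 31 March 2026 | 168 | 2.3 | 2.8 | 1.8 |
| 1 June 2026 | 106 | 1.5 | 1.8 | 1.1 |
| 30 June 2026 | 77 | 1.1 | 1.3 | 0.8 |
| 31 July 2026 | 46 | 0.6 | 0.8 | 0.5 |

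With the earliest permitted visit, d falls by 14 days. Under A the figures become 2.1, 1.3, 0.9 and 0.4.

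**Step 4: the other time points for treatment on 31 March 2026.**

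- Day 14 is 14 April (window 11 to 17 April). This is before any mid-2026 cut, but after the stated study end. For any treatment after 17 March, nominal day 14 falls beyond 31 March.
- Week 12, the other VSS visit, is 23 June (window 13 June to 3 July), so it is borderline at mid-2026.

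**The case against.** A reader might infer that late-enrolled patients will lose their 24-week scar assessment and then be dropped by the complete-case rule. The article does not support that. No text truncates follow-up or sets a data cut. Results keeps the 24-week follow-up alongside the March 2026 enrolment date, and Data Analysis puts the descriptive analyses after data collection. Read together, these passages fit a later analysis with nothing lost at least as well as they fit a loss. This objection stands, and it makes the counts in Step 3 conditional.

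The study period can also be read as the recruitment window, because it is derived from the yearly caseload. That is a fair reading. It would remove the conflict with 31 March 2026 and the figure of about 2 in 10 that goes with it. It does not rescue the mid-2026 date, which conflicts with 24 weeks of follow-up on either reading. The label also has a practical use: Study Data Collection counts five years from the end of the study for the processing of records.

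The word commence could cover a start on the day-14 results while follow-up continues. But the sentence concerns the final analysis, and the article describes no staged analysis.

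Enrolment could finish early enough to make the dates work. The pace makes this unlikely: 4 patients in 374 days, against about 5 per year planned, leaves 6 for the last 355 days.

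Finally, the effect is limited. Only secondary, descriptive 24-week summaries are exposed, missing data are to be reported, and nothing suggests that date of entry is related to scar outcome. This also stands, and it bears on how serious the point is.

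**Conclusion.** The dates are mutually inconsistent as written and need to be reconciled. With enrolment through March 2026, the last week-24 window opens between 2 August and 1 September 2026 and closes between 30 August and 29 September, depending on the day of the last treatment. That is after the stated study end and after any reasonable meaning of mid-2026.

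Loss of 24-week VSS data is a possible consequence, not a stated one. It would follow only if the dates were enforced literally. Under uniform accrual and nominal visit days, it would then affect roughly 2 of 10 patients at a 31 March 2026 cut (1.8 to 2.8) and about 0.5 to 2 of 10 at cuts from 1 June to 31 July (0.5 to 1.8), or slightly fewer if visits are made early in the window. The primary end point is not at risk at a mid-2026 cut. The point is worth correcting, but it does not undermine the design.

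**What to change.** Label 31 March 2026 as the end of enrolment. Set the study end no earlier than the close of the last patient's week-24 window, which is 29 September 2026 if the last treatment is on 31 March. Move the start of the final analysis to after that date. It is safest to state the rule in terms of the last patient's window. Table 1 places the pretreatment visit up to 7 days before treatment, so a patient who consents on 31 March could be treated on 7 April, with a window closing on 6 October.

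No separate day-14 analysis in mid-2026 is needed. It would depart from the rule that analysis follows complete data collection, and in an open-label study it would release results while VSS is still being scored.

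The cost is a date amendment and a later final report: 91 days from 30 June to 29 September, or about three months (60 to 120 days for planned starts from 31 July back to 1 June). No extra patients or visits are needed.

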## Discussion

### Anticipated Findings

The hypothesized key finding of this study is that the combination of RECELL and 3:1 meshed skin grafting will demonstrate both favorable wound healing rates and superior long-term scar quality when compared with historical controls of standard skin grafting techniques for similar large traumatic defects. The management of extensive lower extremity soft tissue and skin loss is often difficult; indeed, several comorbidities should be considered and addressed in these patients [11,15]. The approach is multifactorial and requires commitment from both the surgeon and the patient. Several methods have been developed to address soft tissue and skin coverage of the limbs. For recontraction of large skin defects, the existing literature describes the evaluation, harvesting, transplantation, and management of skin grafting techniques for the lower extremities. Thus, soft tissue defects remain a challenge for orthopedic surgery. Such defects are commonly encountered following orthopedic injuries or infections, and the management of these wounds varies significantly [15,16]. In patients with burns, Elkady et al [17] reported that autologous skin cell suspension (ASCS) with or without split-thickness skin grafting reduced the number of surgical procedures, postoperative complications, and potential cost savings compared with split-thickness skin grafting alone. Carter et al [18] noted that these findings underscore the benefits of integrating ASCS with or without split-thickness skin grafting as a practical approach in burn wound management, providing substantial advantages to both patients and health care institutions. We believe that ASCS with or without split-thickness skin grafting is beneficial for extremity trauma because the wound bed is healthier than that of patients with burns [11,19,20]. However, the role of ASCS with or without split-thickness skin grafting in patients with traumatic skin defects remains unclear. There have been some reports on the use of RECELL in trauma cases [21-24]. The safety profiles were comparable, with similar frequencies of treatment-emergent adverse events of interest observed between the treatment areas. In prior case reports and case series of patients presenting with various nonthermal tissue defect types, ASCS has also shown favorable outcomes related to healing, donor site size, and aesthetic appearance [25-27]. A preliminary study of 10 posttraumatic cases treated with RECELL was conducted in 2020 [9]. This report showed that RECELL could be equivalent to a skin graft with complete healing at 30 days for smaller skin defects (<70 cm²). However, the rate of wound healing decreased to below 13% for larger skin defects (>70 cm²). The authors concluded that RECELL could not be the choice for skin reconstruction of larger traumatic defects and that the best reconstructive option remains traditional split-thickness mesh skin grafts. However, among patients with burns, Holmes et al [28] compared the healing outcomes of RECELL alone (mean area 168.2 cm^2^) and 2:1 meshed skin grafting (mean area 165.0 cm^2^) within-patient allocation of treatments and concluded that both treatment modalities were comparable among 87 patients at 4 weeks postoperatively. Although the target patients differ (trauma and burns) between these studies, the results show conflicting efficacy of RECELL; therefore, it seems premature to investigate the efficacy of RECELL alone in patients with trauma. Therefore, we referred to the prospective, multicenter, randomized trial by Gardien et al [29], who compared mesh grafting alone with grafting with cultured autologous proliferating epidermal cells in patients with burns, found that mesh grafting with cultured epidermal cells was more effective than grafting with mesh alone on postoperative days 5 to 7 in terms of wound closure and scar quality [18]. To investigate the impact of RECELL on early wound closure and scar quality, we designed a treatment protocol for 3:1 split-thickness mesh grafting in combination with RECELL [20,30].

Another key feature of this study is that the participants will not be enrolled unless a good wound bed is prepared. Controlling wound infection is a critical factor that must be addressed in patients with trauma. Kahn et al [31] conducted a randomized open-label trial of RECELL for contaminated diabetic foot gangrene, reporting epithelialization in 66.7% of patients. The key factor influencing this relatively high wound closure rate in diabetic foot gangrene was that the study included patients with skin defects with “adequately vascularized” wounds [31]. As the condition of the wound bed plays a major role in the success or failure of skin grafting, we believe that including this condition in patients with trauma will yield good epithelialization and wound closure.

In the proposed study, we will also investigate postoperative scar formation. However, the observation period will be relatively short (24 weeks). Holmes et al [28] recorded VSS scores for burn injuries with RECELL at 16, 24, and 52 weeks. The authors reported no significant difference between the RECELL and mesh skin grafts throughout the study period. However, we believe that a study period of 24 weeks is sufficient to observe scar formation.

We acknowledge several limitations to this study. First, it is a single-center, open-label pilot study with a small target sample size (n=10), limiting the generalizability of the findings. Second, the lack of a contemporaneous control group means all comparisons with standard care must rely on historical or published data, which introduces inherent bias. However, the data gathered will be essential for calculating the required sample size for a future, adequately powered randomized controlled trial.

### Conclusions

We believe that using RECELL for traumatic skin defects in the extremities will yield better clinical results than using it for patients with burns. With this study protocol, we aim to validate the usefulness of RECELL for skin defects owing to trauma by observing wound closure and scar formation, including adverse events, delayed healing, infection, and durability.
